#### Other Outcomes: Potential Factors Related to HPV Vaccine Hesitancy

To explore the potential factors associated with HPV vaccine hesitancy, our research team has designed a section based on the IMB theoretical framework to assess parents’ HPV-related information, vaccination motivation, and behavioral skills to further explore the factors associated with HPV vaccine hesitancy. We will also directly ask participants what factors can affect their daughters’ HPV vaccination, thereby investigating the reasons for their vaccine hesitancy.

### Blinding

Although participants will not be blinded because of the nature of the intervention, blinded evaluation will be adopted in our study. In this study, all researchers involved in outcome assessments will be blinded to the group allocation. During the intervention, only unblinded research assistants in each center will be aware of the allocation and will be in contact with participants. In addition, all data analysis will be completed by personnel who are blinded to the intervention assignment. Participants will be unblinded after the follow-up survey.

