## Methods

### Trial Design

This will be a double-blind randomized controlled trial (RCT) of an intervention based on an online applet. Before the intervention, the research team will carry out free HPV vaccination pilot projects for 11-13-year-old girls in 4-5 study sites in low-health-resource areas in China. After the first stage of the HPV vaccination program is completed, 11-13-year-old girls’ parents who choose not to vaccinate their daughters will be invited to our intervention study, and those who are willing to participate will be guided to register and log on to the “Yi Yan Health” mini applet (Figure 2), which was independently developed by our research team and can be used for mobile app–based education and questionnaire collection. Next, all participants will be randomly divided into 2 groups: (1) an intervention group, which will receive a baseline questionnaire, 7-day digital HPV vaccination education based on the IMB model (with a sample shown in Figure 3), and follow-up right after the intervention period and 1 week, 1 month, and 3 months after the intervention, and (2) a control group, which will only receive popular science education that is not related to HPV vaccines; these non-HPV publicity materials will be uploaded at the same time every day as the intervention group to maintain parents’ interest in the control group. Meanwhile, participants in the control group will also need to complete questionnaires simultaneously with the intervention group. After the intervention trial, we will provide the control group with the same IMB-based HPV vaccine intervention materials free of charge for ethical considerations. Our free HPV vaccination pilot program will also continue until at least half a year after the intervention to ensure that all 11-13-year-old girls whose parents are willing to vaccinate their daughters can receive the first HPV vaccination during or after the intervention.

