### Recruitment

In 5 regions with free HPV vaccination pilot projects, parents who refuse to vaccinate their daughters and who meet the inclusion criteria will be enrolled into this study. After providing informed consent, all participants will register and log on to the mini applet, and they will then be randomly assigned to the intervention group or the control group in a 1:1 ratio using the randomization algorithm embedded in the mini applet.

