According to the IMB model, digital HPV vaccination education is divided into 3 modules and 6 themes, with each module containing 2 themes. The first module is information, which is the initial prerequisite for promoting healthy behaviors. Module 1 has 2 themes: (1) HPV infection and related diseases and (2) high-risk factors of HPV infection and how to prevent HPV infection. The second module is motivation, which mainly refers to personal attitudes toward health behavior and related social motivation. Personal attitudes include the understanding of HPV susceptibility, the expectation of costs and benefits of taking preventive actions, and the experience and willingness to take actions; social motivation includes social support and social values. Module 2 has 2 themes: (3) introduce the benefits of HPV vaccines so as to encourage parents to vaccinate their daughters and (4) describe the harm and susceptibility of HPV infection through a true story to motivate parents to take action to prevent their daughters from contracting HPV infection. The third module is behavioral skills, which mainly emphasizes the improvement of personal objective skills and self-efficacy. Module 3 has 2 themes: (5) how to use personal objective skills to make firm decisions and communicate effectively with family members to obtain understanding and support for daughters’ HPV vaccination and (6) the concept and function of self-efficacy and ways to improve self-efficacy and promote the transformation of motivation into behaviors.

Each of the 6 thematic courses will be uploaded to the mini applet and will take participants about 10-15 minutes to read and learn. In addition, the mobile app–based HPV vaccination education contains a high level of interactivity with the following learning forms: reading text, viewing pictures, small videos pictures watching, and taking quizzes. The intervention will last for 1 week, and data will be collected at baseline ( 1 week before the intervention); postintervention; and 1 week, 1 month, and 3 months after the intervention. All the data will be obtained for statistical analysis.

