### Adherence

The intervention will be stopped at the participants’ request if they find anything harmful about it, and participants have the right to refuse to answer some sensitive questions in the questionnaire or to withdraw from the study at any time.

Before the intervention, the researchers will introduce the importance and expected benefits of this study. During the intervention, once the course is uploaded, the mini applet will automatically send a text message to participants every day to remind them to learn until they have completed the course. The researchers can also supervise participants by their learning duration, which will be automatically recorded by the backend database of the mini applet. During follow-up, similarly, the mini applet will automatically send a text message to participants every day before they complete the questionnaire, and the number of completed questionnaires will be used to evaluate the adherence of participants to the entire trial process. Finally, we will express our gratitude to all participants for their involvement and encourage them to complete the study through nonmaterial incentives, such as by answering their questions related to HPV or cervical cancer during the research.

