### Limitations

This study has several limitations. First, since HPV vaccines were approved to be used in China in 2016 and have not yet been covered by the National Immunization Program, the sample size cannot be accurately calculated due to the lack of the exact HPV vaccination rate or the HPV vaccine hesitancy rate in central and western China. Second, HPV vaccines need to be administered 2 or 3 times, but the follow-up period may not fully capture the entire vaccination process. As a result, it will be impossible to collect comprehensive data on the frequency and extent of vaccine hesitancy. Third, due to the nature of the intervention, participants in our study will not be blinded and contamination may occur. However, investigators and data analysts will all be blinded to the randomized allocation, and only the research assistants in each center will be aware of the allocation. Fourth, the research sites will be selected by convenience sampling, which would cause selection bias. Although this method is necessary, considering local cooperation and feasibility, it may limit the generalizability of our findings to other regions. Future studies could consider random sampling to enhance representativeness and reduce potential biases.

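### Site assistants who contact parents know the allocation, although no described task clearly needs it, so encouragement could differ between arms

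*Protocol article*

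**What the plan says.** All references are to the protocol article.

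- **Who knows the arm.** Blinding: "During the intervention, only unblinded research assistants in each center will be aware of the allocation and will be in contact with participants". Limitations repeats that "only the research assistants in each center will be aware of the allocation" and counts investigators and analysts as blinded.
- **Parents.** Blinding: "Although participants will not be blinded because of the nature of the intervention, blinded evaluation will be adopted in our study".
- **What the applet does.** Parents are assigned "in a 1:1 ratio using the randomization algorithm embedded in the mini applet" (Recruitment). For the intervention arm, "Each of the 6 thematic courses will be uploaded to the mini applet and will take participants about 10-15 minutes to read and learn" (Intervention Group). For the control arm, "these non-HPV publicity materials will be uploaded at the same time every day as the intervention group" (Trial Design). During the course, "the mini applet will automatically send a text message to participants every day to remind them to learn until they have completed the course" (Adherence), with a similar daily message for the follow-up questionnaires. Questionnaires are self-administered and stored automatically (Data Collection, Management, and Monitoring).
- **What people do.** Adherence adds that "The researchers can also supervise participants by their learning duration". As a non-material incentive, it also offers answers to participants' questions on HPV or cervical cancer during the research.
- **Outcome.** The primary outcome is vaccination within 3 months after the intervention, verified in local health agency records and not self-reported. Outcome assessors and analysts are blinded.

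**The concern.** The trial tests whether a digital course changes a parent's decision to vaccinate. Conversation with project staff can change the same decision. The plan gives knowledge of the arm to the staff who have contact with parents, and it gives no reason. The stated justification, the nature of the intervention, explains why parents cannot be blinded. It does not explain why contact staff are not.

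If an assistant followed up intervention parents more keenly, or spoke more freely about vaccination with them, that would be an unrecorded co-intervention in one arm. The estimated difference would then mix the course with staff encouragement. The Discussion hopes to recommend the course as a convenient, low-cost measure for wider use, and that recommendation depends on crediting the difference to the course itself.

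This is separate from the double-blind label in Trial Design. Correcting the label would leave the staff's knowledge of the allocation as it is.

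**Working it through.** **Step 1. Does any described task need the contact staff to know the arm?**

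| Task | Done by | Arm knowledge needed by site staff? |
|---|---|---|
| Randomisation | Algorithm in the applet | No |
| Delivery, both arms | Uploaded to the applet | No |
| Daily reminders | Automatic text messages | No |
| Questionnaires | Researchers distribute through the applet, to both arms at once; stored automatically | No |
| Supervision by learning duration | Researchers, from the applet's database | Not evidently; completion can be shown without course content |
| Answering HPV questions | Not assigned to a named role | Not evidently; the arm may come out in conversation |
| Stopping at a parent's request | Not assigned to a named role | Not evidently |

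No row clearly requires it. The last three rows show that the automation is not total and that some personal contact is foreseen.

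**Step 2. Do the stated safeguards cover this route?** Registry verification prevents misreporting of vaccination. Blinded assessors and analysts prevent biased assessment and analysis. Neither acts on performance bias: if encouragement leads a parent to vaccinate, the registry correctly records a real vaccination. Limitations names unblinded parents and contamination, but cites the assistants' knowledge as a sign that unblinding is contained.

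**Step 3. The plan's own figure.** Sample Size gives control refusal of 30%, intervention refusal 20% lower, two-sided alpha 0.05, beta 0.2 and 20% dropout. Taking 20% as percentage points (30% against 10%) with unpooled variance:

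n = (1.960 + 0.842)² × (0.3×0.7 + 0.1×0.9) / 0.20² = 7.849 × 0.30 / 0.04 = 58.9, so 59; then 59 / 0.8 = 73.75, so 74 per arm.

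This matches the stated 74. The point disputes no figure; the step only confirms that the planned difference is 20 points.

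**Step 4. Illustration under assumed values.** Assume the course has no effect, while one-sided encouragement lowers refusal by d in the intervention arm. With n per arm, p1 the control refusal, p2 = p1 − d and p̄ their mean:

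- SE0 = √[2p̄(1−p̄)/n]
- SE1 = √[(p1(1−p1) + p2(1−p2))/n]
- chance of a significant result favouring the intervention = Φ[(d − 1.960×SE0)/SE1]

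Example with p1 = 0.30, d = 0.05, n = 375: SE0 = 0.03261, SE1 = 0.03256, (0.05 − 0.0639)/0.03256 = −0.427, and Φ = 0.335.

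| Control refusal | d = 2 points, n = 375 | d = 5 points, n = 375 | d = 5 points, n = 300 | d = 10 points, n = 375 |
|---|---|---|---|---|
| 30% | 8.7% | 33.5% | 27.8% | 88.7% |
| 70% | 8.6% | 30.9% | 25.7% | 82.0% |
| 90% | 13.9% | 54.4% | 45.7% | 97.1% |

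The nominal rate in this direction is 2.5% (5% two-sided). n = 300 is 375 less 20% dropout. The 30% is the plan's figure; 70% and 90% are assumptions, included because every participant has already refused once. The values of d are assumptions throughout. A 5-point shift corresponds to 0.05 × 375 = 18.75, or about 19 vaccinations, and is a quarter of the planned 20-point difference.

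**The case against.** The strongest reply is that no section describes unequal contact. What is described is parallel: the same upload schedule, simultaneous questionnaires, and reminders worded for participants in general. Researchers receive unified training (Settings). The offer to answer HPV questions is made to all participants, so it might dilute the contrast instead of favouring one arm. Unblinded contact staff with blinded outcome assessment are common in behavioural trials, and contact scripts or logs usually sit in a fuller document than a journal article. Parents are unblinded and can reveal their arm anyway.

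Much of this stands. The absence of a script or log is not in itself a fault of the article, and staff blinding could never be complete. Training is mentioned, but the article does not say that it covers equal contact. What the reply does not remove is the arrangement that the article itself fixes: the people in contact know every parent's arm from the start. An occasional disclosure in conversation is a smaller exposure than that.

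Several stronger readings are tempting, and the documents do not support them:

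- **Unequal contact is built in, or staff were unblinded on purpose to encourage one arm.** The text states an arrangement and gives no motive.
- **The unblinded assistants do the supervising.** Adherence says only that researchers can supervise, while Blinding and Limitations treat assistants as a distinct group. Learning duration need not reveal the arm, since both arms receive daily material.
- **Local hospital or vaccination staff know the allocation.** No section says so.

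**Conclusion.** The point holds as a risk that the design leaves open, not as a demonstrated bias. It rests on three things in the text: contact staff know the arm, no described task clearly requires that knowledge, and registry checking with blinded assessment does not protect against differential encouragement.

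Its size cannot be derived from the documents. The illustration assumes that the course has no effect and that the shift falls entirely in one arm. In that case even 2 to 5 points would raise the false-positive rate well above nominal. If the true effect were near the planned 20 points, the same shift would be a tenth to a quarter of it. A reader might infer that a positive result could never be credited to the course; that goes too far. The risk matters most if the true effect is small.

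This is a worthwhile, low-cost improvement and not a defect that invalidates the trial.

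**What to change.** 1. **Blinding and Limitations:** state that arm assignment is visible only to existing central applet personnel who have no contact with participants.
2. **Site assistants:** show them only an arm-neutral completion flag, for example that the day's module has not been opened.
3. **Contact:** use one identical contact script for both arms, covering replies to questions on HPV or cervical cancer as well as reminders.
4. **Adherence:** carry out any supervision by learning duration through the same arm-neutral display, with the same rule for contacting a parent in both arms.
5. **Limitations:** name possible differential staff encouragement, next to unblinded parents and contamination.

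The cost is a change of applet permissions, a short script and some protocol wording. Using existing central personnel is meant to avoid a new post; the article does not describe who administers the applet, so the sponsor should confirm that such personnel exist. There are two downsides. Parents may disclose their arm, so staff blinding will be incomplete. Supervision by course content also becomes more limited than Adherence now allows. The change works best before contact begins; the article reports recruitment as still pending at submission in October 2024.

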### Data Collection, Management, and Monitoring

The questionnaire will be distributed via the mini applet, and all completed questionnaires will be automatically saved into the read-only web-based database to ensure authenticity of the data. Moreover, our researchers will promptly check the collected data after each questionnaire survey. Regarding integrity of the data, all questions will be self-administered and set as mandatory to ensure that all submitted questionnaires have no missing data.

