#### Primary Outcome: HPV Vaccination Status

The ultimate goal of this study is to improve the HPV vaccination rate among 11-13-year-old girls. This indicator will be measured by the proportion of parents who choose to vaccinate their daughters against HPV within 3 months after the intervention. To ensure the authenticity of HPV vaccination, the vaccination status will be checked by the registration history in the information systems of local health agencies, which have already collaborated with us, rather than being self-reported by participants. The HPV vaccination behaviors will be strictly verified by our researchers, and those who are just “willing” to be vaccinated will not be included in the positive results.

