### Statistical Analysis

Stata 16.0 will be used for statistical analysis. The distribution of categorical variables will be described by frequencies and percentages, and continuous variables conforming to normal distribution will be described by means (SDs). Chi-square tests will be performed to compare the differences between different groups. The *t* test or 1-way ANOVA will be performed to compare the mean scores between groups on the same continuous and dependent variables. Logistic regression will be conducted to analyze the factors associated with HPV vaccine hesitancy. Repeated measurement data at baseline; postintervention; and 1 week, 1 month, and 3 months after the intervention will be analyzed using generalized estimation equations (GEEs). Significant variables will be included in baseline chi-square analysis, and we will also assess group (intervention and control), time (baseline; immediately after the intervention; and 1 week, 1 month, and 3 months after the intervention), and time×group interactions, with the interaction indicating a differential change by group from baseline to the end of the trial. Statistical significance will be set at *P*<.05 (2-sided).

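### Every questionnaire item is mandatory, yet parents may refuse sensitive items; as written, a refusal becomes a lost wave or an arbitrary answer on the hesitancy outcomes

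*Protocol article*

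**What the plan says.** Two sections of the protocol article set rules for answering the questionnaire.

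- **Data Collection, Management, and Monitoring:** every item is self-administered and "set as mandatory to ensure that all submitted questionnaires have no missing data". What is stored is described as follows: "all completed questionnaires will be automatically saved into the read-only web-based database". Nothing is said about partly completed forms.
- **Adherence:** "participants have the right to refuse to answer some sensitive questions in the questionnaire or to withdraw from the study at any time".

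The questionnaire carries the secondary outcomes (general vaccination attitude, HPV vaccine hesitancy, vaccine confidence) and the IMB-related factors. It is given at baseline, after the intervention, and at 1 week, 1 month and 3 months. Under Statistical Analysis, mean scores are compared between groups by t test or one-way ANOVA. The repeated measurements go into a GEE with group, time and "time×group interactions, with the interaction indicating a differential change by group from baseline to the end of the trial". No working correlation is named there.

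The primary outcome has a separate source: "the vaccination status will be checked by the registration history in the information systems of local health agencies".

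**The concern.** The two rules cannot both operate unless the form offers a way to decline, and none is described. Without one, a parent who uses the right to refuse a single item has two routes. The parent can leave the form unsubmitted, so the whole wave is lost, or can enter any answer to get past the item. In the first case an item refusal becomes a missing questionnaire. In the second a false value enters the database and looks complete. No later analysis can recover either one.

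This matters more here than in most trials. Under Eligibility Criteria, every participant has already refused the vaccine for a daughter. The questions a parent may find sensitive are plausibly those on hesitancy and attitudes, which are the secondary outcomes. The arms also differ in what they see: one receives seven days of HPV content ending in an invitation to vaccinate, the other unrelated material, and participants are not blinded. Refusal could therefore be related to hesitancy, and more strongly in one arm. If the more hesitant parents drop out of the intervention arm's responses, the mean score among those remaining improves without any effect of the education.

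**Working it through.** **1. The two rules side by side**

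| Situation | Mandatory items | Right to refuse | Result as written |
|---|---|---|---|
| Parent answers everything | satisfied | not used | complete wave |
| Parent declines one item, form has no decline option | not satisfied | used | wave not submitted |
| Parent enters an arbitrary answer | satisfied | lost in practice | complete but false |
| Parent selects a decline option | satisfied | used | submitted, one item blank |

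Only the last row honours both rules, and the article does not describe it. The completeness statement is true of submitted forms only.

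**2. How large could a bias be?** The plan gives no figure on this point. The only input from it is the 20% dropout allowance (Sample Size). The rest are assumptions: no true effect; correlation ρ = 0.6 between baseline and 3-month score; baseline score B standard normal; loss in the intervention arm with probability p(B) = 1/(1 + exp(-(a + B))), that is, log-odds 1 per SD; loss in the control arm unrelated to the score.

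The mean baseline score of those retained in the intervention arm is -E[B·p(B)]/(1 - d), where d is the loss fraction. For a standard normal B, E[B·p(B)] = E[p(1 - p)]. The available-case difference at 3 months is ρ times that mean.

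- d = 20% in each arm: a = -1.65 and E[p(1 - p)] = 0.1386. Then -0.1386/0.80 = -0.173, and 0.6 × -0.173 = **-0.104 SD**. Large simulations gave -0.105 to -0.107.
- d = 25% in the intervention arm, 15% in control: a = -1.31 and E[p(1 - p)] = 0.1599. Then -0.1599/0.75 = -0.213, and 0.6 × -0.213 = **-0.128 SD**. Simulation gave -0.127.
- Adjusting for the baseline score: -0.002 to +0.001 SD.

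**3. The same two scenarios through a five-occasion group × time GEE** (200,000 per arm)

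| Loss | Independence | Exchangeable (correct) |
|---|---|---|
| 20% / 20% | -0.105 | -0.001 |
| 25% / 15% | -0.124 | -0.004 |

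If the true correlation is of autoregressive type, so that exchangeable is misspecified, the estimate is +0.03 to +0.04: small, and against the intervention.

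**4. A second set at the planned size** (375 per arm, assumed true effect -0.30 SD, within-person correlation 0.5, about 17 to 20% of follow-up forms lost, 60 runs per cell, simulation SE about 0.01)

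| What drives loss | Independence | Exchangeable |
|---|---|---|
| Nothing (completely random) | -0.31 | -0.30 |
| Arm only (30% vs 10%) | -0.31 | -0.30 |
| Baseline score, one arm | -0.39 | -0.30 |
| Current, unobserved score, one arm | -0.47 | -0.39 |

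Unequal loss between arms does no harm by itself. Loss driven by baseline hesitancy matters only when the analysis ignores the baseline score. Loss driven by the current, unseen score biases both versions, by 0.09 to 0.17 SD in this example.

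**The case against.** The strongest reply is that a mandatory item need only receive a response, and a 'prefer not to answer' choice is a response. The items themselves are not shown, so such a choice may exist. This is fair: the loss of a whole wave follows from the text as written and is not an established fact about the applet. But the article does not describe the choice, and stating it would resolve the conflict.

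It can also be said that the plan does not deny loss of whole questionnaires. The completeness claim covers submitted forms only, 20% dropout is allowed for, and daily reminders and completion counts are planned. That stands too. The fault is that the statement gives reassurance on data integrity while leaving out the route by which refusals disappear.

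Three stronger readings are tempting and not supported:

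- **That the planned GEE is valid only if loss is completely random.** Loss that depends on arm alone is harmless, since arm is in the model. With a correctly specified working correlation, loss that depends on the observed baseline score is also handled.
- **That the false-positive rate is about 25% or 34%.** Those rates follow from the two differences in step 2 at 300 per arm. They apply only to an available-case comparison or an independence GEE under the assumed one-arm mechanism.
- **That GEE must give way to a mixed model, weighting or imputation.** That choice is commonly left to an analysis plan, which is not shown. A mixed model would not cure loss driven by the unobserved current score either.

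Finally, the simulated mechanism is general dropout related to hesitancy, not item refusal. It shows what such loss could do and does not measure the harm from the conflict between the two rules.

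**Conclusion.** The conflict between mandatory items and the right to refuse is real and unreconciled. It concerns how data are collected, so it should be settled before the baseline questionnaire is issued. Its reach is limited to questionnaire outcomes; the primary outcome rests on health agency records.

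The statistical consequence is conditional. If loss rises with baseline hesitancy in one arm only, an available-case t test or an independence GEE is biased by about -0.1 SD under the assumptions in step 2. The bias is near zero with baseline adjustment or a correctly specified exchangeable correlation. These figures are illustrative, because the documents give no evidence on which parents would refuse items or stop responding.

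**What to change.** 1. Reconcile the two sections. Add a 'prefer not to answer' response to the sensitive items so that the form can still be submitted, and say so in both places. If the applet already has one, state it.
2. Limit the completeness statement: every item in a submitted form has a response, which may be a recorded refusal, and unsubmitted forms remain missing.
3. In Statistical Analysis, use the baseline score already collected. Replace the unadjusted comparison of follow-up means with a baseline-adjusted one, or state that the GEE uses a working correlation other than independence. GEE can stay.

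The cost is one option on the form and a few sentences. The downside is a small number of item-level blanks that the scoring must handle. Step 3 does not protect against loss driven by the current, unobserved score; step 1 helps there to the extent that parents who would otherwise abandon the form submit it instead.
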